### Study procedures

Table 1 gives an overview of the clinical and radiological evaluations the patient will encounter in both centers following written informed consent. The physiotherapy will be performed by the patient’s physiotherapist according to the study-specific rehabilitation protocol. This physiotherapy protocol is based on five phases. Proceeding to the next phase depends on the patients rehabilitation progress and not on the post-operative time.

**Table 1 Tab1:** Pre-, intra- and post-operative clinical and radiological evaluations

Timepoint	Clinical and radiological evaluations
Pre-operative	Pre-rupture: Tegner score, Lysholm score and IKDC score Post-rupture: VAS pain, knee function, Lachman test, EQ-5D-5 L, isokinetic and proprioceptive measurement, and MRI
Intra-operative	Knee function, pivot shift test, surgery time and complications
Post-Operative	
Day 1	VAS pain, return to work rupture-surgery interval, EQ-5D-5 L and complications
Week 2	VAS pain, return to work, knee function, EQ-5D-5 L and complications
Week 6	VAS pain and satisfaction, mobilization with crutches, return to work, return to sports, knee function, Lachman test, EQ-5D-5 L, complications and X-ray knee
Week 13 (3 months)	VAS pain and satisfaction, mobilization with crutches, return to work, return to sports, knee function, Lachman test, EQ-5D-5 L, Tegner score, Lysholm score, IKDC score, complications, and isokinetic and proprioceptive measurement
Week 26 (6 months)	VAS pain and satisfaction, return to work, return to sports, knee function, Lachman test, EQ-5D-5 L, Tegner score, Lysholm score, IKDC score, complications, number of physiotherapy and orthopaedic surgeon consults, single leg and triple leg hop test, isokinetic and proprioceptive measurement, and MRI
Week 52 (1 year)	VAS pain and satisfaction, return to work, return to sports, knee function, Lachman test, EQ-5D-5 L, Tegner score, Lysholm score, IKDC score, complications, number of physiotherapy and orthopaedic surgeon consults, single leg and triple leg hop test, triple crossover hop and drop jump test, isokinetic and proprioceptive measurement, and MRI
Week 104 (2 years)	VAS pain and satisfaction, return to work, return to sports, knee function, Lachman test, EQ-5D-5 L, Tegner score, Lysholm score, IKDC score, complications, number of physiotherapy and orthopaedic surgeon consults, and MRI

*IKDC* International Knee Documentation Committee, *MRI* magnetic resonance imaging, *VAS* visual analogue scale

MRI is performed on a 3 T system (Magnetom Prisma Tim, Siemens, Erlangen, Germany) for IBLA and ACL reconstruction arms. For patients treated by DIS, a 1.5 T system (Magnetom Aera Tim, Siemens, Erlangen, Germany) with metal artefact reduction sequences will be used. The 4-level Howell classification, originally proposed for grading ACL graft, is adapted for evaluating the repaired ligaments [44]. The morphology and signal intensity of the ACL graft or repair will be subjectively assessed on conventional MRI [45].

When re-surgery is needed or a failure occurs, the patient is not excluded from the study and the follow-up will continue according to this protocol. Under re-surgery, we consider all surgeries a patient undergoes on the side of the injured knee affecting his/her mobility. Re-surgery following re-rupture will be considered as a failure.

If the proximal ACL rupture is not suitable for repair, the patient will undergo an ACL reconstruction (exploratory group). These patients will be followed according to this protocol except for the post-operative MRI measurements on week 52 and 104, and the post-operative isokinetic measurements on week 13, 26 and 52 as these measurements are study-specific and not standard of care.

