#### Secondary endpoints

Pain experienced by the patients as measured by Visual Analogue Scale (VAS) pain score [30, 31].Overall functioning by the patient, related to the knee, as measured by Tegner and Lysholm score [32].Health-Related Quality of Life (HRQoL) as measured by EQ-5D-5 L [33, 34].Time to recovery as measured by mobilization with crutches, return to work and sports.Patient satisfaction towards the surgery and revalidation level as measured by VAS satisfaction.Mechanic functioning of the knee as measured by Lachman test; single leg hop, triple leg hop, triple crossover hop and drop jump test; proprioceptive measurement; isokinetic measurement; and knee function [35–42].Intra- and post-operative complications: adverse device effects (ADEs) and serious adverse events (SAEs).Success of the operation techniques defined as the number of non-failures.
A failure is defined as:
A re-rupture of the graft or the repaired ACL: clinically and MRI-confirmedInstability complaints: AP translation difference of more than 3 mm (Lachman test) between the injured knee and the contralateral knee, and subjective instability complaints [17].The number of physiotherapy and (extra) orthopaedic surgeon consults.ACL healing will be evaluated with MRI [43].

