#### Analysis of the secondary outcomes

To evaluate robustness of the results a sensitivity analysis of the primary outcome will be done using different analysis sets.Analysis set without failures: patients that have a failure within the 6 months of follow-up are excluded from this analysisAnalysis set without re-surgeries: patients that have a re-surgery within the 6 months of follow-up are excluded from this analysisIn case we are not able to show superiority between the arms, we will consider non-inferiority between the arms. To this end we will choose 10 IKDC points as non-inferiority margin (see Hoogeslag et al. [25]). Non-inferiority will be considered in the different analysis sets and only be concluded if they give similar findings. The analysis sets considered here are intention-to-treat, the analysis set without failures and the analysis set without re-surgeries.As the IKDC scores are measured at many different time points during the patient’s follow-up we can compare the evolution over time between the treatment arms using a linear mixed model. Also here we will consider the effect of failure and re-surgery through inclusion and exclusion of the results after failure.Linear regression will be performed on the changes from baseline to 24 months in the continuous outcomes like VAS pain, VAS satisfaction, Tegner score, Lysholm score, EQ-5D-5 L, Lachman test, single leg and triple leg hop test, triple crossover hop and drop jump test, isokinetic and proprioceptive measurement and knee function. The evolution over time of these continuous outcomes will be compared between the different treatments using a linear mixed model.A survival analysis with log-rank test will be used to compare the time to return to work and time to return to sports between the different treatment arms. The time from the surgery until the patient is mobile without crutches will be analysed in the same way.The number of physiotherapy/orthopaedic surgeon consults will be compared between the different treatment arms using linear regression.The morphology and signal intensity of the ACL will be assessed with MRI and compared between the different treatments using a Chi-square test at the different time points.

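### The MRI system is set by treatment, so a DIS difference in MRI grade cannot be attributed to healing; formal MRI tests belong in study 2 only

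*Protocol article*

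**What the plan says.** The protocol article, under Study procedures, fixes the imaging by treatment: "MRI is performed on a 3 T system (Magnetom Prisma Tim, Siemens, Erlangen, Germany) for IBLA and ACL reconstruction arms", whereas "For patients treated by DIS, a 1.5 T system (Magnetom Aera Tim, Siemens, Erlangen, Germany) with metal artefact reduction sequences will be used". In the same place it introduces the grading scale: "The 4-level Howell classification, originally proposed for grading ACL graft, is adapted for evaluating the repaired ligaments". It also describes how images are read: "The morphology and signal intensity of the ACL graft or repair will be subjectively assessed on conventional MRI".

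Under Secondary endpoints, "ACL healing will be evaluated with MRI" is listed, and the abstract counts MRI among the main secondary outcomes. Table 1 places post-operative MRI at weeks 26, 52 and 104.

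Under Analysis of the secondary outcomes, morphology and signal intensity are to be "compared between the different treatments using a Chi-square test at the different time points". The DIS contrasts are not excepted. No common acquisition, calibration between systems or adjustment for scanner is described.

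**The concern.** Study 1 randomises between DIS and IBLA. Every DIS image comes from one field strength and sequence set, and every IBLA image from another. The outcome is a subjective reading of signal and shape, which may depend on how the image was acquired. A difference in grade could reflect healing, the machine, or both, and the trial data cannot say which. The non-randomised DIS versus reconstruction comparison has the same problem on top of its existing limits.

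At stake is a main secondary outcome. A formal p-value for DIS versus IBLA would carry the authority of a randomised comparison that the imaging does not support.

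A second, smaller matter is efficiency. The only categorical MRI scale named has four ordered levels, and a chi-square test ignores the order.

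**Working it through.** **1. Patients available.** The Sample size section gives a difference of 13, SD 13, alpha 0.025, power 80% and 10% dropout. The exact two-sided t-test calculation gives 20.3, so 21 per arm (power 81.5% at 21). Then 21 / (1 - 0.10) = 23.3, so 24. The stated 21 and 24 are reproduced. No MRI power figure is given, so 21 to 24 per arm is what the MRI comparison has.

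**2. Which comparisons are confounded.**

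| Comparison | Systems | Scanner and treatment |
|---|---|---|
| DIS vs IBLA (study 1) | 1.5 T with artefact reduction vs 3 T | coincide completely |
| DIS vs reconstruction (across studies) | 1.5 T with artefact reduction vs 3 T | coincide completely |
| IBLA vs reconstruction (study 2) | 3 T vs 3 T | same system |

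Let T = 1 for DIS and S = 1 for the 1.5 T system. A model for the grade is a + bT + cS. Because S = T for every patient, this equals a + (b + c)T. Only b + c can be estimated. The covariates the protocol offers (age, gender, working category, Tegner score) do not change this, and pooling both studies does not help, because the 1.5 T indicator is still the DIS indicator.

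**3. What a scanner effect could do.** The article gives neither a grade distribution nor a scanner effect, so both are assumed. Three IBLA distributions over the four grades were used: 25/25/25/25, 40/30/20/10 and 50/30/15/5%. A fraction m of DIS scans is read one grade higher, with no true difference. Example with 40/30/20/10 and m = 0.3:
- grade 1: 0.40 × 0.7 = 0.28
- grade 2: 0.30 × 0.7 + 0.40 × 0.3 = 0.33
- grade 3: 0.20 × 0.7 + 0.30 × 0.3 = 0.23
- grade 4: 0.10 + 0.20 × 0.3 = 0.16

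Simulated chance of p < 0.05 at 21 to 24 per arm (6,000 runs per scenario):

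| DIS scans shifted | Chi-square | Ordinal test |
|---|---|---|
| 20% | about 7% | 7-11% |
| 30% | 7-12% | 9-18% |
| 50% | 13-30% | 19-43% |

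At 240 per arm, a 30% shift gives p < 0.05 by chi-square in 49-88% of runs. This is bias, and more patients do not cure it. An ordinal test picks up a scanner shift somewhat more often than chi-square, so a change of test is no remedy for the confounding.

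**4. Choice of test where the comparison is sound.** Assumptions: four ordered grades, a common odds ratio of 3, two-sided 0.05, 21 to 24 per arm, baselines 25/25/25/25 and 40/30/20/10%, and shifts in either direction. Power is about 27-37% with chi-square and 43-54% with a rank test. For a non-monotone difference (25/25/25/25 versus 10/40/40/10%, 24 per arm) the order reverses: 42% with chi-square and 6% with the rank test.

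**The case against.** **The implants differ too.** DIS uses a spring-screw implant in the tibia; IBLA uses a tape with a femoral button and a bone anchor (Study intervention). The mention of artefact reduction suggests an implant-related reason for the separate system, though the article gives none. Scanning both study 1 arms on one machine would therefore remove the machine part of the confounding and leave any implant artefact. This stands, and it is why a common scanner is not the main remedy.

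**Timing.** Inclusion began in February 2018 and the article appeared in November 2019, so many week-26 scans should already exist. A switch now would mix systems within the IBLA arm and within patients over time. This also stands.

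**Unknown size.** No scanner effect is quantified, and with 20% of scans shifted the false-positive rate is only about 7% by chi-square. That is fair. It limits any claim about how wrong the result will be, but it does not make the two effects separable.

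**Chi-square is a matter for the analysis plan.** The article names the test but does not say outright that it is run on the Howell grade, and a plan that is not shown may refine it. The test is also valid: with no difference, simulated rejection was about 3-5% despite small expected counts. What remains is an efficiency point.

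**Stronger readings the documents do not support.** A reader might infer that an arm-specific scanner unblinds patients at week 26, when the primary IKDC is collected. Nothing says patients know the field strength or what it implies, and the order of MRI and questionnaire within that visit is not given. A reader might also infer that the primary result is affected because re-rupture is MRI-confirmed. Patients with failures stay in the primary analysis, and nothing shows that the scanner alters that confirmation.

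**Conclusion.** The confounding follows from the stated design and needs no assumption. For DIS versus IBLA and DIS versus reconstruction, scanner and treatment are inseparable, so a difference in MRI grade cannot be attributed to healing. The size and direction of the scanner effect are unknown. The false-positive rates of 7-12% and 13-30% by chi-square rest on assumed misgrading of 30% and 50% of DIS scans and on assumed grade distributions.

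The scope is limited to the DIS contrasts of one secondary endpoint. The MRI comparison in study 2 is like for like as to system, and the primary IKDC analysis and its sample size are untouched.

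The test choice is a separate, minor point. An ordinal method gains about 16-17 percentage points of power (43 - 27 = 16; 54 - 37 = 17) for a consistent shift at an odds ratio of 3, provided the Howell grade is what is tested. Even then power is only about one half.

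**What to change.** 1. Report MRI findings for DIS versus IBLA and DIS versus reconstruction descriptively, as grade counts per arm and time point, without p-values. State that system, sequences and implant artefact all differ with the treatment.
2. Confine formal MRI tests to IBLA versus reconstruction in study 2.
3. As a separate, minor change, analyse the ordered 4-level grade in study 2 with a Wilcoxon rank-sum test or a proportional-odds model. The downside is lower power for a non-monotone difference.
4. Optional, where feasible: acquire study 1 post-operative images in both arms on the 1.5 T system with the same sequences. This removes only the machine part of the confounding. It would lower the field strength for those IBLA images, make the exploratory early versus late IBLA contrast cross scanners, and mix systems if introduced part-way. DIS contrasts should stay descriptive even so.

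Items 1 to 3 cost wording only and need no extra scans or patients. What is given up is a formal DIS test on MRI whose result could not have been interpreted as a healing effect.

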### Study duration

The start date of inclusion is February 2018, expected end date of inclusion is June 2020. The follow-up duration is 2 years. Last patient follow-up visit is expected in June 2022.

### Sample size

The primary outcome is change in IKDC score from baseline (pre-rupture) to 6 months post-operatively. A difference in IKDC change score of 13 points between the treatment arms is considered clinically meaningful as described by Irrgang et al. and Collins et al. [46, 47]. In order to detect an effect of 13 IKDC points with 80% statistical power between any of the two treatment arms using an independent samples t-test in which alpha is 0.025 (alpha corrected for the fact that per study data set 2 tests will be performed), assuming a standard deviation of 13 on the change in IKDC score per arm (SD found in pilot study), we need 21 patients per arm. Taking into account a drop out of 10%, we need 24 patients per arm or 48 patients in total which have to be randomized.

In study 1, 24 patients per arm (DIS and IBLA) will be included and in study 2, 24 patients per arm (IBLA and ACL reconstruction) will be included. The total number of patients to be included is 96. We expect that 50% of the patients will be included in Antwerp University Hospital and 50% in University Hospital Brussels. We also expect that the total number of addressed patients will range from 96 to 106, since we expect that about 10% of the patients will not have a repairable, proximal ACL rupture. They will not be eligible (any more) after the intra-operative confirmation and these patients (exploratory group) will not contribute the number of 96 patients needed for inclusion.

### Randomization and blinding

Randomization will take place when the patient is diagnosed with an acute ACL rupture, which is MRI confirmed, fits all the in- and exclusion criteria (expect for the two inclusion criteria which are intra-operatively confirmed: proximal and repairable ACL rupture), and when the patient has signed the informed consent. The randomization procedure will be generated in Castor Electronic Data Capture software (Castor EDC, Amsterdam, the Netherlands). Castor uses stratified block randomization. Randomization will be stratified according to center. Per center a permuted block randomization with variable block size will be used.

The LIBRƎ study is a single-blind study meaning that the treating physicians (principal and sub-investigators) and the study coordinator are not blinded. The patient and the patient’s physiotherapist are blinded.

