**Methods:**

Subjects, aged 18–50 years, with a proximal, primary and repairable ACL rupture will be included. DIS is preferably performed within 4 weeks post-rupture, IBLA within 12 weeks and reconstruction after 4 weeks post-rupture. Patients are included in study 1 if they present within 0–4 weeks post-rupture and surgery is feasible within 4 weeks post-rupture. Patients of study 1 will be randomized to either DIS or IBLA. Patients are included in study 2 if they present after 4 weeks post-rupture and surgery is feasible between 5 and 12 weeks post-rupture. Patients of study 2 will be randomized to either IBLA or reconstruction. A total of 96 patients will be included, with 48 patients per study and 24 patients per study arm. Patients will be followed-up for 2 years. The primary outcome is change from baseline (pre-rupture) in International Knee Documentation Committee score to 6 months post-operatively. The main secondary outcomes are the EQ-5D-5 L, Tegner score, Lysholm score, Lachman test, isokinetic and proprioceptive measurements, magnetic resonance imaging outcome, return to work and sports, and re-rupture/failure rates. The statistical analysis will be based on the intention-to-treat principle. The economic impact of the surgery techniques will be evaluated by the cost-utility analysis. The LIBRƎ study is to be conducted between 2018 and 2022.

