**Fig. 1 Fig1:**
[figure not shown]
Study flow diagram: screening, inclusion, surgery and follow-up. *Depends on when the patient presents at the consultation desk after the ACL rupture. **Patients in the exploratory group will be replaced, but are still part of the study. ACL = Anterior Cruciate Ligament, DIS = Dynamic Intraligamentary Stabilization, IBLA = Internal Brace Ligament Augmentation, MRI = Magnetic Resonance Imaging

Allocation to either study 1 or study 2 depends on the patient’s admission time point after ACL injury and if it is practically feasible to perform ACL surgery within 4 weeks. There is a patient and referral delay, a magnetic resonance imaging (MRI) needs to be performed to confirm the ACL rupture and the surgery has to be planned. On the other hand, inclusion and surgery between week 5–12 after injury is expected to be more manageable to plan. There will be an intra-operative confirmation in study 1 and study 2 of the ACL’s eligibility for repair. If the proximal ACL rupture is not suitable for repair, ACL reconstruction will be performed. To keep the three arms (DIS, IBLA and the conventional reconstruction arm) comparable, patients with a non-repairable proximal ACL rupture will be replaced by a new patient even if they were randomized to the conventional ACL reconstruction. These patients will be seen as excluded from the randomized medical device (but not excluded from the study) and will undergo a conventional ACL reconstruction (exploratory group). These patients will be treated as a sub-population and will not be included in the primary analysis.

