### Study population

#### Inclusion criteria

Primary acute proximal ACL rupture: 3-digit ACL rupture classification, type A (MRI and intra-operative confirmation) [17] (Fig. 2).Age: 18–50 years.Presented and planned surgery within 4 weeks after the ACL rupture (Study 1).Presented and planned surgery between 5 and 12 weeks after the ACL rupture (Study 2).The ACL remnant is suitable for repair in the three treatment arms: at least 75% of the distal ACL remnant must be in contact with the proximal remnant/femoral condyle (intra-operative confirmation).Mentally and verbally capable of participating in the study.Written informed consent (according to the ICH-GCP Guidelines).

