### Statistical analyses

#### Analysis of the primary outcome

To answer the research question comparing the three treatment arms the research question is split up in three separate questions:
*Is there a difference between DIS and IBLA (≤4 weeks)?*

Results from study 1 will be used in a linear regression model with IKDC at 6 months as outcome and treatment, and IKDC at baseline as predictors. This linear regression model will allow correction for possible confounders like age, gender and working category.
*Is there a difference between IBLA (5–12 weeks) and conventional ACL reconstruction?*

Results from study 2 will be used in a linear regression model with IKDC at 6 months as outcome and treatment, and IKDC at baseline as predictors. This linear regression model will allow correction for possible confounders like age, gender and working category.
*Is there a difference between DIS and conventional ACL reconstruction?*

Results from study 1 and study 2 will be compared using a linear regression model with IKDC at 6 months as outcome and treatment, and IKDC at baseline as predictors. As this is a non-randomized comparison this model will correct for possible confounders like age, gender and working category.

For the primary analysis all patients that didn’t have a repairable, proximal ACL rupture will be excluded from the analysis (exploratory group). Patients with a failure or re-surgery will be included in the primary analysis.

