The ideal scenario would have been to include the ACL reconstruction group in Study 1 and defer the ALC reconstruction until 5 weeks post-injury, but this is a design choice we did not make for several reasons. The DIS technique has to be performed within 4 weeks post ACL rupture and ACL reconstruction after the knee has regained its function, often after 4 weeks post ACL rupture. IBLA can be performed up to 12 weeks post ACL rupture. If ACL reconstruction would be performed within the 4 weeks this would not be according to clinical practice. If the patients in Study 1 would have to be recruited in a 3 instead of 2 arms comparison, 78 patients would have to be recruited within the 4 weeks after ACL rupture. Due to patient and doctors referral delay, many of the patients with a ruptured ACL report to our orthopaedic departments after 4 weeks and therefore could not be included in the 3 arm comparison. We expected the early patient group (0–4 weeks) to be more challenging to recruit compared to the 5–12 weeks post rupture group; 78 patients within 0–4 weeks would substantially prolong the inclusion period. Patient blinding would be more difficult as patients can easier guess which treatment they received depending on the rupture-surgery time. For both the 0–4 and 5–12 weeks groups, after inclusion a date of surgery will be chosen, afterwards the randomization will be performed. If first the randomization will be performed and afterwards the date of surgery is chosen with the patients, it could give a clue which type of surgery the patient will receive. Hence, we decided to organize our study according to the principle: randomize each patient to the possible treatment options at the time of presentation post-rupture, corresponding with common clinical practice.

Ahmad et al. conclude in their systematic review paper that there is sufficient evidence to support that DIS repair may be an effective modality for the treatment of acute proximal tears of the ACL [48]. However, comparative studies are lacking. Upcoming studies should compare the technique to ACL reconstruction with failure as an endpoint. Comparison to rigid methods of proximal fixation is also necessary to justify the need for dynamic fixation. In the LIBRƎ study, the aforementioned points are compared. Overall, there is evidence to suggest the potential space for ACL repair in the decision tree for individualized treatment planning.

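### Repairability is judged after randomisation by unblinded surgeons and then decides who enters the primary analysis, so that set is not intention-to-treat and can depend on the arm

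*Protocol article*

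**What the plan says.** Four parts of the protocol article bear on this.

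- **Timing.** Under Randomization and blinding, a patient is randomised who "fits all the in- and exclusion criteria (expect for the two inclusion criteria which are intra-operatively confirmed: proximal and repairable ACL rupture"). The Discussion gives the order: "after inclusion a date of surgery will be chosen, afterwards the randomization will be performed".
- **Who judges, and how.** Inclusion criteria sets the repairability threshold: "at least 75% of the distal ACL remnant must be in contact with the proximal remnant/femoral condyle (intra-operative confirmation". Rupture location is checked by MRI and again at surgery. Randomization and blinding states that "the treating physicians (principal and sub-investigators) and the study coordinator are not blinded".
- **What follows from the judgement.** Study design (text below Fig. 1) says that "patients with a non-repairable proximal ACL rupture will be replaced by a new patient even if they were randomized to the conventional ACL reconstruction". The stated reason is to keep the arms comparable. These patients receive a reconstruction and form an exploratory group. Analysis of the primary outcome repeats that those without a repairable, "proximal ACL rupture will be excluded from the analysis (exploratory group").
- **The label.** The Abstract says: "The statistical analysis will be based on the intention-to-treat principle". Analysis of the secondary outcomes also lists an intention-to-treat set among the three sets that must agree before non-inferiority is concluded.

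**The concern.** Randomisation protects a comparison only if membership of the analysed set does not depend on the arm. Here membership is decided after allocation, by a person who is not blinded.

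In study 2 the judgement has unequal consequences. In the IBLA arm, finding a remnant non-repairable changes the operation to a reconstruction. In the reconstruction arm the ruptured ligament is removed either way (Study intervention), so the verdict alters only the patient's status in the trial. A surgeon who knows the arm has more reason to examine a marginal remnant closely before a repair. If marginal remnants leave the IBLA arm more readily, that arm keeps the better tissue and its mean IKDC rises. The Background itself links successful repair to tissue quality.

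In study 1 both arms are repairs. The two techniques might prompt different verdicts on a marginal remnant, but nothing in the article indicates which arm would gain.

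No stated analysis would reveal the problem. The two extra sets in Analysis of the secondary outcomes remove failures or re-surgeries, and no set is stated to bring the excluded patients back.

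**Working it through.** **The plan's own figures.** Inputs from Sample size: difference 13, SD 13, alpha 0.025 (taken as two-sided), power 80%, drop-out 10%, about 10% non-repairable.

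- Normal approximation: n = 2 × (2.241 + 0.842)² × (13/13)² = 19.0, so 20 per arm.
- t-test: n = 20.3, so 21 per arm, with power 81.5% at 21. This matches the plan.
- Drop-out: 21/0.9 = 23.3, so 24. This matches.
- Patients addressed: 96 × 1.1 = 105.6, so 106 as stated. Dividing instead gives 96/0.9 = 106.7, so 107. The difference is immaterial.

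The point contests none of these figures.

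**Analysed set against the label.** The exploratory patients are randomised, remain in follow-up, and are outside both the 96 and the primary analysis. An analysis that omits randomised patients on a finding made after allocation is not intention-to-treat in the usual sense.

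**Illustrative size.** The article gives no exclusion rate by arm and no relation between remnant quality and IKDC, so both are assumed. Let a share f of one arm, the lowest on judged repairability, be excluded, with no selective exclusion in the other arm. Let ρ be the correlation of that judgement with 6-month IKDC change in the affected arm. Then

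bias = ρ × SD × φ(z_f) / (1 − f), with SD = 13.

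- f = 0.10: φ(−1.282)/0.90 = 0.1755/0.90 = 0.195, and × 13 = 2.53 points per unit of ρ.
- f = 0.20: φ(−0.842)/0.80 = 0.280/0.80 = 0.350, and × 13 = 4.55 points per unit of ρ.

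| f in one arm | ρ | Bias (IKDC points) | Two-sided type I error (nominal 0.025) |
|---|---|---|---|
| 10% | 0.3 | 0.76 | 0.028 |
| 10% | 0.5 | 1.27 | 0.032 |
| 20% | 0.3 | 1.36 | 0.033 |
| 20% | 0.5 | 2.27 | 0.048 |

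Type I error is from the noncentral t with 21 per arm. At the 10-point non-inferiority margin, with an assumed one-sided alpha of 0.025 and ρ = 0.5, the false non-inferiority rate would be 0.049 (f = 10%) or 0.080 (f = 20%).

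In patients, f = 10% is about 3 exclusions from one arm (24/0.9 = 26.7) and f = 20% is 6 (24/0.8 = 30). The standard error of the difference is 13 × √(2/21) = 4.0 points. The illustrated bias is thus below the sampling error, but a larger trial would not remove it.

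**The case against.** The other side has good points.

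- *The rule applies to every arm.* Non-repairable patients in the reconstruction arm are replaced too. A reader might infer that this arm keeps everyone, but the text says the opposite. What remains is that an equal rule does not give equal application when the assessor knows the arm.
- *The criterion is pre-specified and numeric.* The 75% threshold, and MRI as well as surgical assessment of location, limit discretion. They do not remove it near the threshold.
- *Remnant quality may matter little once the ligament is removed.* If so, keeping marginal patients in the reconstruction arm barely moves that arm's mean. That is fair if the target is only the patients the repairing surgeon accepts. If the target is everyone meeting the written criterion, dropping marginal remnants from IBLA still raises the IBLA mean.
- *The exclusion is open and rests on a condition present before treatment.* True, and it would be defensible if judged without knowledge of the arm. The article does not provide for that. A fuller protocol might, but what is stated here is randomisation first, unblinded physicians, then exclusion.
- *Unequal exclusions disturb block balance.* This is minor: a difference of a few patients does not invalidate a regression comparison.

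A reader might also infer a bias favouring repair in both randomised comparisons. The documents do not support that, because study 1 has no reconstruction arm.

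**Conclusion.** The point stands. The primary set is chosen after randomisation, by people who may know the arm, and it is not the intention-to-treat set that the Abstract names. In study 2 the likely direction favours IBLA; in study 1 the direction is unknown.

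The size cannot be derived from the article. The range of about 0.8-2.3 points rests on selective exclusion of 10-20% in one arm only and ρ of 0.3-0.5, all assumed. It is 6-18% of the 13-point target (0.8/13 to 2.3/13) and 8-23% of the 10-point margin, so it matters more for a non-inferiority claim than for superiority.

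A reader might put the bias as high as 4 points, for example by multiplying a 20-percentage-point gap in exclusion by a 20-point IKDC deficit. The documents support neither input. Excluding 20% from all three repair arms and none from reconstruction averages (3 × 20% + 0%)/4 = 15%, above the roughly 10% expected. A 20-point deficit exceeds the trial's whole meaningful difference. Nor do the documents show that any bias has occurred; they show that the design permits it.

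**What to change.** **Patients still to be enrolled.** Release the Castor allocation to the surgeon only after rupture type and remnant contact have been recorded and locked in the eCRF. The surgery date is already set before randomisation, so scheduling and patient blinding need not change. The targets of 21 evaluable and 24 randomised per arm also stay as they are. The costs are a protocol amendment, having materials for both techniques ready at each operation (reconstruction must already be available as the fallback), and a change of procedure part-way through. The article appeared in November 2019, about 21 months into a recruitment period of about 28 (February 2018 to June 2020), so this reaches only the later patients.

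**Patients already randomised.**

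1. Report the number excluded as non-repairable or non-proximal by arm and by study.
2. Add a sensitivity analysis of 6-month IKDC with all randomised patients as allocated. It needs no new data: Study procedures drops only some MRI and isokinetic measurements for the exploratory group.
3. Require this set, beside the three already listed, for any non-inferiority conclusion. It should not replace them, because excluded patients receive a reconstruction whatever their arm, which pulls the arms together. With an assumed 10% affected, 13 points becomes at most 0.9 × 13 = 11.7. Power is then about 72% with 21 per arm or 79% with 24.
4. Describe the primary set as modified intention-to-treat, and state the exclusion wherever intention-to-treat is now named.
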